### Study population

#### Inclusion criteria

To be eligible, patients must meet the following inclusion criteria: they must be able to identify a primary caregiver via a specific questionnaire and must consent to complete this (if patients are unable to identify their caregiver themselves due to their disease, a form for self-designation as primary caregiver will be available); patients must be aged 60 years or older and residing in the region of Burgundy-Franche-Comté; they must have recently been diagnosed in hospital or in a private-sector medical practice with one or more of the following diseases: local or metastatic cancer diagnosed within the previous 6 months (breast cancer in first-line chemotherapy treatment, hormone-sensitive prostate cancer, colorectal cancer in first-line chemotherapy treatment); neurodegenerative disease (Parkinson’s disease diagnosed within the previous 5 years, Alzheimer’s or similar diseases diagnosed within the previous 12 months), AMD, (geographic atrophy or neovascular AMD, diagnosed within the previous 12 months, with an acuity range of between 2 and 6/10, aged 65 years or older and able to complete the Mini-Mental State Examination (MMSE) test); heart disease (heart failure diagnosed within the previous 3 months); neurovascular disease (ischemic or hemorrhagic stroke with clinical evidence of post-stroke lesions more than 24 h old, diagnosed within the previous 6 months and with a Rankin score ≤ 2).

*The eligibility criteria of principal caregivers* are as follows: they must be members of the patient’s social environment (family, friend or neighbor); they must be identified by the patient as the “primary caregiver” based on the designation questionnaire or they must have completed the self-designation form as primary caregiver; they must be aged 18 years or older; they must not be employees of a health care organization; they must be residing in the region of Burgundy-Franche-Comté; and they must be able to complete the study questionnaires.

#### Noninclusion criteria

Any patient who has been previously diagnosed with another targeted disease and/or those living in a retirement home will not be included. Principal caregivers who are under guardianship, curatorship or under the protection of justice will be excluded.

#### Inclusion procedure

Inclusion will be performed in two steps. First, patients will be identified, during a clinical consultation in the context of a diagnosis for one of the diseases being investigated, by clinicians involved in the ICE cohort study who had participated in the reflection phase on inclusion strategies for the different diseases, the procedures to recruit caregivers and the logistic support to set up. At the first consultation, which is a medical visit planned at hospital within the scope of the patient’s pathology, the clinician will indicate the presence or not of a potential informal primary caregiver. They will ask the patient to come to the next consultation with their caregiver (the timetable is defined according to the inclusion strategy, depending on the patient’s pathology). Then, at the second consultation, two possibilities for the inclusion of informal caregivers exist, namely patients are either accompanied by their caregiver or they attend unaccompanied. If the patient comes to the second consultation with their caregiver, as requested, both the patient and their caregiver will be informed of the study, complete the identification questionnaire with the health care facility CRA involved in the study, and receive the Consent Form. Alternatively, if the patient does not attend the consultation with his caregiver, then the caregivers will be contacted by phone based on the information provided by the patient in the identification questionnaire. An appointment will be made with the caregivers to present the study to them and to give them the relevant information concerning the study (information sheet) and the Consent Form. If patients are unable to identify their primary caregiver by themselves due to their health status, a self-designation form as primary caregiver will be proposed to the person(s) accompanying the patient (Figs. 1 and 2).

**Fig. 1 Fig1:**
[figure not shown]
Scenario 1: patients are accompanied by their caregiver. Caregivers’ inclusion according to scenario 1: patients are accompanied by their caregiver

**Fig. 2 Fig2:**
[figure not shown]
Scenario 2: patients are alone. Caregivers’ inclusion according to scenario 2: patients are alone

#### Randomization procedure

Once all the caregivers’ inclusion questionnaires have been completed (during the month following inclusion) and collected by the CRA, randomization will be performed for each group of diseases using a minimisation technique. Minimization will be stratified, regardless of the disease group, according to center, age (80 years or older versus below 80 years) and gender. Additional specific stratification factors are:For cancers: cancer localization (breast, prostate, colorectal), stage (nonmetastatic and resectable versus advanced or metastatic)For Alzheimer’s disease: stage of disease (very early stage (MMSE score ≥ 26) versus mild (20 ≤ MMSE score < 26) versus moderate (10 ≤ MMSE score < 20) versus severe (MMSE score < 10))For Parkinson’s disease: stage of severity of Parkinson’s disease (stages I to V according to the Hoehn and Yahr classification) [19]For heart failure: severity of disease (according to the New York Heart Association (NYHA) classification)For neurovascular diseases: Rankin Score: (nondependent Rankin ≤ 2 or dependent Rankin > 2)For AMD: form of AMD, namely geographic atrophy versus neovascular disease

Caregivers randomized to the intervention arm will receive an information booklet and will receive support provided by a social worker scheduled every 6 months for 2 years (from 6 to 24 months after inclusion). The duration of the support will be 1 h per visit and will be defined in two parts: firstly, administration of the Linear Analogue Scale Assessment quality of life (LASA) questionnaire, and secondly, a standardized semidirective interview to assess needs. The LASA questionnaire will serve as a support tool for the intervention to detect any health problems and optimize the responses provided by the social worker [20]. LASA includes four HRQoL dimensions, namely global quality of life, mental wellbeing, physical wellbeing, and level of fatigue and, using a Visual Analogue Scale (VAS) ranging from 0 (worst HRQoL level imaginable) to 10 (best HRQoL level), assesses the caregiver’s perception of their own health status. The social worker will then conduct a semidirective interview to evaluate the caregiver’s needs and to detect any early signs of burn-out.

In the control arm, caregivers will only receive the information booklet. This booklet will inform caregivers about existing structures and support programs. Nevertheless, caregivers randomized to the control arm retain the possibility to solicit the social services participating in the study on their own initiative, or other appropriate services, for social support if needed.

### Sample size calculation

#### Observational and interventional studies

The calculation of the number of caregivers required was based on both the design and the primary objectives of the intervention study, with noncompetitive recruitment according to each group of diseases (randomization performed 1:1 per group). We aim to demonstrate the efficiency of the intervention in each of the five groups of diseases. The hypothesis is that the intervention proposed will improve the HRQoL of caregivers on at least one of the two summary scores of the MOS SF-36 (i.e., physical health and/or mental health).

The minimal clinically important difference (MCID), which is the smallest change in an outcome that a patient would identify as important, was fixed at 5 points [21].

The null hypothesis (H0) is that there will not be a difference of at least 5 points between the two arms in at least one HRQoL summary score at 1 year; while the alternative hypothesis (H1) is that there will be a difference of at least 5 points between the two arms in at least one HRQoL summary score at 1 year.

With a bilateral alpha risk of 5 % and a statistical power of 90 % to detect a difference of at least 5 points (standard deviation (SD) = 25), and adjusted to take account of the number of statistical tests and maintain an overall alpha type one error rate of 5 % (Bonferroni adjustment):With two dimensions of HRQoL, α’ = α/2 = 0.05/2 = 0.025With five groups of diseases, α” = α’/5 = 0.025/5 = 0.005 (cancer (breast, prostate, colorectal); neurodegenerative disease (Alzheimer’s disease and similar diseases); AMD; neurovascular (stroke); cardiac (heart failure))At least 1684 caregivers should be randomized in each disease group. However, we anticipate lower recruitment in the heart failure group. Accordingly, only 488 caregivers will be randomized (bilateral α type I error of 0.005 and statistical power of 80 %) to demonstrate a difference of at least 5 points (SD = 15). Thus, it will be necessary to include and to randomize 4 × 1684 = 6736 caregivers, plus 488 in the heart failure group, representing a total of 7224 caregivers. An interim analysis will be planned to reject either H0 or H1 (Alpha Spending Function and O’Brien-Fleming Boundaries) when half the caregivers have been included with 1 year of follow-up in each of the subgroups. To allow for 5 % of loss to follow-up, it will be necessary to include and randomize an additional 380 caregivers, resulting in an overall total of 7604 caregivers (1750 caregivers for each of the four large groups of diseases and 604 for the heart failure group)

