#### Analysis

Analyses will be performed using SAS (version 9.4) (SAS Institute Inc., Cary, NC, USA), R (version 3.2.2) [49] and Stata (v13) (StataCorp LP, TX, USA) software. The statistical analysis plan for the primary and secondary objectives will be written before the database is locked.

All analyses will be on a modified intention-to-treat principle, i.e., including all randomized informal carers regardless of the eligibility criteria and intervention received, with MOS SF-36 scores available at baseline and 1 year. Analyses for the interventional study will be done on an intention-to-treat basis. After Bonferroni adjustment, statistical significance will be fixed at the 0.005 level for primary analyses, and at the 0.05 level for the secondary objectives.

An interim analysis is planned when half of the patients will be included to reject or not H0 (efficacy) or H1 (futility); the Alpha Spending Function with O’Brien-Fleming Boundaries will be used to determine the alpha-level significance at the interim and at the final analysis using EAST® software (Cytel Software Corporation, Cambridge, MA, USA) [50]. The corresponding confidence interval will be computed (1 − alpha level).

Sociodemographic and clinical characteristics will be described at inclusion using frequency (percent) for qualitative variables and mean (SD), or median (min–max) for continuous variables. Data will be compared between randomization arms using the Student *t* test or the nonparametric Mann-Whitney test, or analysis of variance (ANOVA) or the Kruskal-Wallis test for continuous variables and the Chi-squared or Fisher’s exact tests for qualitative variables, as appropriate. Scores will be described at each follow-up time point using mean (SD) and median (min–max) in each arm.

After describing missing data and investigating the mechanism of missing data profiles, imputation will be performed using a multiple imputation method by sensitivity analysis after checking normality, and univariate and multivariate ANOVA adjusted for baseline score will be performed to compare the two summary scores of the SF-36 questionnaire at 1 and 2 years.

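### The written hypotheses turn on a 5-point difference, but the sample size and the planned test address a null of zero difference

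*Protocol article*

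**What the plan says.** All places are in the Protocol article.

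- **Sample size calculation, Observational and interventional studies.** The MCID "was fixed at 5 points". The null follows: "The null hypothesis (H0) is that there will not be a difference of at least 5 points between the two arms", on at least one of the two summary scores at 1 year. The alternative is its complement: "the alternative hypothesis (H1) is that there will be a difference of at least 5 points between the two arms".
- **Same section, the four large disease groups.** The trial is sized with a "statistical power of 90" % "to detect a difference of at least 5 points (standard deviation (SD) = 25"). Alpha is Bonferroni-adjusted to 0.005 for two scores and five disease groups, which gives 1684 caregivers per group, randomized 1:1.
- **Same section, heart failure.** 488 caregivers, with SD 15, the same 5 points, and a "bilateral α type I error of 0.005 and statistical power of 80" %.
- **Analysis.** The summary scores are compared by ANOVA adjusted for baseline, and "statistical significance will be fixed at the 0.005 level for primary analyses". No margin or shifted null appears. A confidence interval at one minus the alpha level is planned.
- **Analysis, interim.** "An interim analysis is planned when half of the patients will be included to reject or not H0 (efficacy) or H1 (futility"), with an alpha spending function and O'Brien-Fleming boundaries.

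**The concern.** Taken literally, the pair of hypotheses is a margin hypothesis. True differences of 1, 3 or 4 points all belong to H0, and rejecting H0 would support the claim that the difference is at least 5 points. A test of that H0 would have to be built around 5 points. The sample size and the ANOVA look like those of an ordinary comparison against zero.

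If so, the test cannot support the conclusion that the written hypotheses attach to it. The hypotheses govern both the final conclusion in each disease group and the interim efficacy decision, which is itself phrased as rejecting H0. Having some effect and having an effect of at least the MCID are different claims for a trial meant to inform support policy for caregivers.

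**Working it through.** **Inputs** (Sample size calculation and Analysis): planning difference 5; SD 25 with 90% power (four large groups) or SD 15 with 80% power (heart failure); two-sided alpha 0.005, so z = 2.807; 1:1 allocation; stated totals 1684 (842 per arm) and 488 (244 per arm).

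**1. Reproduce the stated sizes under a null of zero.** n per arm = 2 × (z for alpha + z for power)² × SD² / 5².

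- Large groups: 2 × (2.807 + 1.282)² × 25² / 5² gives 836 per arm, 1672 in total. The exact t calculation gives 1676. Stated: 1684.
- Heart failure: 2 × (2.807 + 0.842)² × 15² / 5² gives 240 per arm, 480 in total. The exact t calculation gives 484. Stated: 488.

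The stated figures lie within 2% of these (12/1672 = 0.7%; 8/480 = 1.7%). Power of the zero-null test at the stated sizes is 90.3% and 80.9%. The sizes are those of a zero null with power evaluated at 5 points.

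**2. Smallest observed difference that is significant.** SE = SD × √(2/n per arm); threshold = 2.807 × SE.

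- Large groups: SE = 25 × √(2/842) = 1.218; threshold = 3.42 points.
- Heart failure: SE = 15 × √(2/244) = 1.358; threshold = 3.81 points.

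Both thresholds are below 5.

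**3. How often the test rejects when the written H0 is true.** P(reject) = 1 − Φ(2.807 − d/SE) for a true difference d; the opposite tail is negligible at these values.

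| True difference | Large groups | Heart failure |
|---|---|---|
| 3 points | 36.5% | 27.5% |
| 4 points | 68.3% | 55.5% |
| just under 5 | approaches 90% | approaches 81% |

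For a zero null these are ordinary power values. Read against the written H0 they would be type I error rates, far above 0.005.

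**4. What the planned interval would show.** At an observed difference of exactly 5, the 99.5% interval is 5 ± 3.42 = 1.6 to 8.4 (large groups), or 5 ± 3.81 = 1.2 to 8.8 (heart failure). Even then a difference of at least 5 points is not shown.

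These figures are for a single analysis, without the interim look or the baseline adjustment. At the interim, fewer data and a stricter boundary require a larger observed difference, but crossing the boundary still rejects zero and not the written H0.

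**The case against.** The best reply is that the design is clear in practice. The main objective is to compare the summary scores between arms, 5 points serves as the detectable difference, the ANOVA is a plain comparison at 0.005, and no margin is set anywhere. The H0/H1 sentence reads like the MCID carried over into the hypothesis wording. This stands as to what was probably meant, and it shows that sample size and method need no change. It does not rescue the sentence. The 5-point wording is in both hypotheses, directly after the MCID is fixed, and the heart failure calculation speaks of demonstrating such a difference. The interim decision rule then refers to those hypotheses by name.

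A reader might infer more than the document supports:

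- **That significant results will be reported as proof of a 5-point benefit.** No section states a conclusion or reporting rule, so this is only a risk created by the wording. The planned interval at one minus alpha would let a reader see that 5 points is not established; what is absent is a statement of how to read it against 5.
- **That the trial is badly underpowered.** A test of the written H0 would reject only 0.25% of the time at a true 5 points. No such test is planned, so the figure shows only that the literal wording cannot be what was meant.
- **That the stated sizes could arise only from a zero null.** The same sizes would fit a 5-point margin if the true difference were about 10 points (5 + (2.807 + 1.282) × 1.218 = 9.98 in the large groups). The document assumes no difference larger than 5, so this is no defence of the wording.
- **That interim futility has no reference value.** H1 as written already ties futility to 5 points. Only the efficacy half, rejection of H0, has the defect.

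**Conclusion.** The point holds as a mismatch between the stated hypotheses and the rest of the design. The size calculation and the ANOVA address a null of zero with 5 points as the planning difference; the written H0 covers everything below 5. A significant result, interim or final, would reject zero only. At the final analysis that can happen from about 3.42 points observed (3.81 in heart failure), and at a true 4 points it would happen about 68% of the time (56% in heart failure).

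These numbers assume the protocol's own SDs, the stated sizes fully evaluable, and a single unadjusted comparison at 0.005. Baseline adjustment or the interim look would shift the thresholds somewhat but would not turn the test into one of a 5-point margin. Severity is moderate: the hypotheses need correcting, while the sample size and the analysis method are not at fault on this point.

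**What to change.** For each disease group and each summary score:

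- Restate H0 as a difference of zero between arms at 1 year and H1 as a difference not equal to zero. Name 5 points (the MCID) as the planning difference used for power.
- State that a significant test alone does not show a benefit of at least 5 points, and that this is judged by where the confidence interval already planned under Analysis lies relative to 5.
- When H1 is restated, say explicitly that interim futility is assessed against the 5-point design alternative; otherwise the restatement would remove the link to 5 that the present H1 provides.

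Sample size, alpha and test are unchanged. The cost is a wording amendment, best made before any interim look, and a more modest claim from a significant result.

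### The heart failure group is sized with SD 15 after SD 25 was applied to the same outcome in all five groups; the only reason given, lower recruitment, has no bearing on the SD, and the stated 80% power depends on it

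*Protocol article*

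**What the plan says.** All of this is in the protocol article, under Sample size calculation (Observational and interventional studies), with the significance level repeated under Analysis.

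- The aim is to show the effect separately in each of five disease groups, on at least one of the two SF-36 summary scores at 1 year. The minimal important difference "was fixed at 5 points" for every group.
- The general calculation asks for "statistical power of 90 % to detect a difference of at least 5 points (standard deviation (SD) = 25". Alpha is divided by two scores and five groups to give 0.005, and heart failure is listed among the five. The result is 1684 caregivers in each disease group.
- Heart failure is then treated separately: "However, we anticipate lower recruitment in the heart failure group. Accordingly, only 488 caregivers will be randomized". The inputs for that figure are a "bilateral α type I error of 0.005 and statistical power of 80" per cent, "to demonstrate a difference of at least 5 points (SD = 15".
- After an allowance for 5% loss to follow-up, the section gives 1750 for each of the four large groups and 604 for heart failure.
- The Analysis section confirms that "statistical significance will be fixed at the 0.005 level for primary analyses", with no separate level for heart failure.

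**The concern.** Outcome, target difference, alpha and 1:1 allocation are the same in all five groups. Two inputs change for heart failure: power falls from 90% to 80%, and the SD falls from 25 to 15. The text links the change to expected recruitment. That is a legitimate reason to accept a smaller group, and with it lower power or a larger detectable difference. It is no reason to expect less variable scores. The article gives no other basis for SD 15, and it had just applied SD 25 to this same group.

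The conclusion for a whole disease group rests on this. If SD 25 is the better value, a non-significant heart failure result carries little information about a 5-point effect, although the protocol labels the test as having 80% power. If SD 15 is the better value for all groups, the four large groups are planned at nearly three times the size they need.

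**Working it through.** **Inputs from the protocol article.** Difference 5 points; two-sided alpha 0.005; 1:1 allocation; SD 25 and 90% power for the general calculation; SD 15 and 80% power for heart failure; stated totals 1684 and 488; final heart failure number 604 with 5% loss.

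**Formula.** Per arm, n = 2 × (z₀.₉₉₇₅ + z_power)² × (SD/5)², with z₀.₉₉₇₅ = 2.807, z₀.₈₀ = 0.842 and z₀.₉₀ = 1.282. Powers below are for a two-sample t test (noncentral t), on one score, without covariate adjustment, at a single final analysis.

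**1. Reproduce the plan's figures.**
- SD 25, 90% power: 2 × (4.089)² × 25 ≈ 836 per arm, total 1672. The plan says 1684 (0.7% higher), which gives 90.2% power.
- SD 15, 80% power: 2 × (3.649)² × 9 ≈ 240 per arm, total 480. The plan says 488 (1.6% higher), which gives 80.5% power.

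Both figures stand on their own inputs.

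**2. Where the reduction comes from.**
- SD 25, 80% power: 2 × (3.649)² × 25 ≈ 666 per arm, total 1332.
- Lowering power at SD 25 therefore saves 1672 − 1332 = 340 caregivers.
- Changing SD from 25 to 15 saves 1332 − 480 = 852.

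Most of the cut comes from the SD.

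**3. Heart failure power for 5 points across the SD range.** The standard error of the difference is SD × √(2/n per arm). At SD 25 with 244 per arm it is 2.263, so 5/2.263 = 2.209, well short of the critical value of about 2.81. The 574 column is 604 × 0.95 = 573.8, or 287 per arm. SDs 18 and 20 are not in the protocol; they are assumptions to show the range.

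| SD | 488 evaluable | 574 evaluable |
|---|---|---|
| 15 | 80.5% | 87.9% |
| 18 | 59.8% | 69.5% |
| 20 | 47.7% | 57.0% |
| 25 | 27.2% | 33.7% |

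With all 604 evaluable, power at SD 25 is still only 36.0%.

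**4. Difference detectable with 80% power at SD 25.**
- 488 evaluable: 3.649 × 2.263 ≈ 8.3 points.
- 574 evaluable: 3.649 × 25 × √(2/287) = 3.649 × 2.087 ≈ 7.6 points.

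**5. The opposite case, SD 15 in every group.** 90% power needs 2 × (4.089)² × 9 ≈ 301 per arm, total 602. Against 1684, that is 1082 fewer per group, or 4 × 1082 = 4328 fewer over the four large groups. With 1684 caregivers and SD 15, power exceeds 99.9%.

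**The case against.** The strongest reply is that nothing is hidden or miscalculated: the article states both SDs and the lower power, and 488 follows from SD 15. That stands. A reader might infer a sample size error, and the document does not support that.

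A reader might also infer that the heart failure test simply has 27% power, or that the two SDs cannot both be true of one endpoint. Neither follows. The groups are caregivers of different patient populations, randomized and tested separately, and their scores could vary to different degrees. The article does not claim that they do, and does not show which SD is right.

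The low-power figures are also conservative in three ways.

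- **Final number.** The plan ends at 604, so about 34% is nearer to the planned group than 27%. (604 is not 488 inflated for 5% loss, which gives about 514; that is a separate matter.)
- **Baseline adjustment.** The Analysis section adjusts for baseline score. With an assumed baseline to 1-year correlation of 0.5 to 0.6 (not given in the article), SD 25 acts like about 21.7 to 20. Power is then about 40% to 48% with 488, and 48% to 57% with 574. This applies to every group, so it does not explain a smaller SD in one. Going from 25 to 15 by adjustment alone would need a correlation of √(1 − (15/25)²) = 0.8.
- **Two scores.** Success is possible on either summary score. If both improved by 5 points and were independent, a favourable assumption, the chance of at least one success at SD 25 is 1 − (1 − 0.272)² ≈ 47% with 488 and 1 − (1 − 0.337)² ≈ 56% with 574.

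Each of these softens the size of the shortfall. None brings power at SD 25 to 80%, and none supplies a reason for the change of SD. An article may leave the source of an SD to the full protocol, so a missing citation is not the point. The point is that the reason it does give has no bearing on the SD.

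**Conclusion.** The concern holds as an unexplained inconsistency between two planning assumptions for one outcome. The heart failure group's 80% power depends on SD 15, which departs from the SD 25 applied to that same group just before, and expected recruitment does not account for the change.

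The size depends on which SD is right. At SD 25, unadjusted power per score is about 27% with 488 evaluable or 34% with 574, and 80% power is reached only at about 8.3 or 7.6 points. At SD 15 the heart failure figure is sound, but if that SD applied to all groups, about 602 caregivers per group would give the 90% power for which 1684 are planned. These figures assume alpha 0.005 two-sided, equal arms, one score, no covariate adjustment and no interim look.

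The inconsistency does not affect type I error, bias or the analysis of the other groups. It bears on how large the groups should be and on how a null heart failure result may be read.

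**What to change.** Either use one SD for the SF-36 summary scores in all five groups, or keep SD 15 for heart failure and justify it from data. The 2013–2015 feasibility study described under Trial status is one place to look, if it yielded usable scores.

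In either case, restate heart failure power at the number actually planned across SD 15 to 25, together with the detectable difference at SD 25. For example: with 574 evaluable caregivers, unadjusted power per score for 5 points is about 88% at SD 15 and 34% at SD 25, and at SD 25 the difference detectable with 80% power is about 7.6 points. If the sponsor wants credit for baseline adjustment, the assumed correlation should be stated and applied to every group.

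The cost is wording, and possibly a less favourable stated power for one group. No extra enrolment is needed. The group need not be relabelled as estimation only: that would give up one of the five planned demonstrations and reopen the five-way division of alpha, and the Analysis section already provides for a confidence interval matched to the adjusted alpha.

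### The 5 % loss allowance is divided wrongly between disease groups: heart failure is set at 604 where 5 % loss gives 514 (the total of 7604 is right)

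*Protocol article*

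**What the plan says.** All figures are in the Protocol article, Sample size calculation (Observational and interventional studies), unless noted.

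- **Large groups.** The inputs are "With a bilateral alpha risk of 5 % and a statistical power of 90 % to detect a difference of at least 5 points", with "standard deviation (SD) = 25". After Bonferroni division by two scores and five groups, alpha is 0.005. The result is a minimum of 1684 caregivers per group.
- **Heart failure.** Lower recruitment is expected here, so the requirement is reduced to 488. The inputs are "bilateral α type I error of 0.005 and statistical power of 80" per cent, "to demonstrate a difference of at least 5 points (SD = 15").
- **Sum before loss.** 4 × 1684 + 488 = 7224.
- **Loss.** One rate is given, 5 %. On that basis, "it will be necessary to include and randomize an additional 380 caregivers, resulting in an overall total of 7604 caregivers", and the group targets follow in parentheses: "1750 caregivers for each of the four large groups of diseases and 604 for the heart failure group".
- **Structure.** Recruitment is noncompetitive by disease group, with "randomization performed 1:1 per group", and the stated aim is to show the effect in each of the five groups. The Analysis section confirms that "statistical significance will be fixed at the 0.005 level for primary analyses".

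**The concern.** The group targets add up to the correct total, so the paragraph looks consistent at first reading. Yet the smallest group receives the largest share of the allowance: heart failure goes from 488 to 604 (116 more), and each large group from 1684 to 1750 (66 more). A single loss rate cannot produce both increments.

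A correct total does not settle the matter, because the trial is sized and tested by group and a surplus in one group cannot make up a shortfall in another. Two things are at stake. The heart failure target asks for more caregivers than its own assumptions need, in the group the protocol expects to be hard to recruit. The reader also cannot tell whether the heart failure design is 488 evaluable at 80 % power or something larger.

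**Working it through.** **Inputs.** Difference 5 points; two-sided alpha 0.005; 1:1 allocation; SD 25 and power 90 % (large groups); SD 15 and power 80 % (heart failure); loss 5 %. All are stated in the Sample size calculation section.

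**1. Reproduce the requirement before loss.** Normal approximation, n per arm = 2 × (z₁₋α/₂ + z_power)² × (SD/difference)², with z₀.₉₉₇₅ = 2.807.

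- Large group: 2 × (2.807 + 1.282)² × 25, rounded up to 836 per arm, 1672 in all (t-test 1676). Stated: 1684.
- Heart failure: 2 × (2.807 + 0.842)² × 9, rounded up to 240 per arm, 480 in all (t-test about 483). Stated: 488.

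Both stated figures are slightly above the formula (0.7 % and 1.7 %), and the article does not say why. They are close enough to accept as the protocol's own requirement, and the rest of the check uses them.

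**2. Reproduce the total.** 4 × 1684 + 488 = 7224. Then 7224/0.95 = 7604.2, and 7604 − 7224 = 380. Both match. Multiplying instead gives 7224 × 1.05 = 7585, so the protocol used N/(1 − 0.05).

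**3. Apply the same rule by group.**

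| | Required | N/0.95 | Printed | Loss implied by printed figure |
|---|---|---|---|---|
| Each large group | 1684 | 1772.6, so 1773 | 1750 | 1 − 1684/1750 = 3.8 % |
| Heart failure | 488 | 513.7, so 514 | 604 | 1 − 488/604 = 19.2 % |

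N × 1.05 would give 1769 and 513, so the choice of formula does not explain the printed figures. The printed figures do sum correctly: 4 × 1750 + 604 = 7604.

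Of the 380 extra caregivers, 4 × 66 = 264 go to the large groups and 116 to heart failure. A proportional split is about 89 for each large group and 26 for heart failure.

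**4. Evaluable numbers and power at 5 % loss.** Normal approximation, two-sided alpha 0.005.

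- Heart failure: 604 × 0.95 = 573.8, about 86 above 488. Power is 88.2 % (t-test 87.9 %), against 80.9 % at 488. The target exceeds 514 by 90, and 90/514 = 17.5 %.
- Each large group: 1750 × 0.95 = 1662.5, about 22 below 1684 (1.3 %). Power is 89.8 % (t-test 89.7 %), against 90.3 % at 1684.

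**5. Corrected total.** 4 × 1773 + 514 = 7606. With 1774 for equal arms, 4 × 1774 + 514 = 7610.

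**The case against.** The strongest reply has three parts.

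- **The text applies 5 % to the total, not to each group.** The split then appears in parentheses, and 7604 − 4 × 1750 = 604 exactly. The heart failure figure may therefore be the remainder after the large groups were set at a round 1750. This fits every printed number, although the article does not say it. It would explain how 604 arose, but it does not justify it: the requirement, the alpha and the aim are all set by group, and no higher loss rate is given for heart failure.
- **The heart failure error is on the safe side.** This stands. No test loses validity, power is above plan, and the burden of about 90 extra caregivers is not quantified anywhere.
- **The large-group shortfall is negligible.** This also stands. Half a point of power is lost and the result still rounds to 90 %. Measured against the formula (1672 or 1676) rather than the stated 1684, the gap is only 10 to 14 caregivers.

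Two stronger readings are tempting and are not supported. A reader might infer that 604 is a leftover from a calculation at 90 % power and SD 15, because that size is 602 by normal approximation and 606 by t-test. Neither equals 604, the article states 80 % power for this group, and the exact remainder is a simpler account. A reader might also infer that the wrong targets shift the closing of each group or the timing of its interim analysis. The article gives no rule for closing a group, and it does not say whether half the caregivers is counted from the numbers before or after the loss allowance.

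**Conclusion.** The group split is wrong as printed; the total is right. The material part is heart failure: 604 against 514, which corresponds to 19.2 % loss instead of 5 % and to about 88 % power instead of 80 %. The shortfall of about 22 evaluable caregivers in each large group is a minor by-product. It would be an overstatement to say that four of the five groups are underpowered, since they keep about 89.8 %.

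Severity is minor: no hypothesis, alpha level, endpoint or test is affected. The conclusion rests on three assumptions: the stated 1684 and 488 are the required evaluable numbers, the single 5 % rate applies to every group, and lost caregivers do not contribute to the 1-year comparison. The last is what a loss allowance presupposes.

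**What to change.** Restate the group targets as 1773 for each large group (1774 if the two arms are to be equal) and 514 for heart failure, with a total of 7606 (7610). This changes the printed total by 2 to 6 caregivers and needs only a correction of numbers.

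If 604 is intended for heart failure, say which power or loss rate it represents and separate it from the 5 % calculation. The large-group figure should still be corrected from 1750 to 1773. The total would then be 4 × 1773 + 604 = 7696 (7700 with 1774), which is 92 to 96 more than the printed 7604.
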